#### Study population

We intend to assess selected counties, selected facilities and clients receiving services from the selected facilities. For the county assessment, the study population will be the 47 counties from which we have selected 12 counties—4 implementing autonomy reforms, 4 planning to implement and 4 controls. For the facility assessment, the study population will be all county-owned public facilities within the selected counties across all level 2-6 of service provision level 2 (dispensaries), level 3 (health centers) level 4, 5 and 6 (hospitals) (table 1). Level 1 in Kenya comprises community health services, these will be excluded as at the time of the protocol, there were minimal to no mechanisms for payment for services provided at that level. For the client exit interviews, the study population will be all patients or carers whose patients had received services from the selected facilities on the day and time of the survey. These will include patients or carers seeking services such as outpatient services, antenatal services, postnatal services, child welfare services, management of chronic illness and maternity services and those discharged from inpatient care.

**Table 1 T1:** Selected counties with distribution of facilities

Group	County	Level 2	Level 3	Level 4	Level 5	Level 6	Total facilities in county
Controls	Tana River	44	5	3	0	0	52
	Migori	115	19	14	0	0	148
	Embu	88	9	4	1	0	102
	Kirinyaga	47	22	4	0	0	73
Already implementing	Makueni	189	39	12	0	0	240
	Mombasa	40	8	4	1	0	53
	Nakuru	140	26	17	1	0	184
	Kajiado	81	21	5	0	0	107
Intervention	Kakamega	111	48	12	1	0	172
	Lamu	29	3	3	0	0	35
	Homabay	120	48	16	0	0	184
	Nyandarua	54	24	2	0	0	80
	Total by level	1058	272	96	4	0	1430

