**Figure 1 F1:**
[figure not shown]
Theory of change. PHC, primary healthcare.

The immediate outputs expected from the inputs and activities include timely decision-making, enhanced community participation in facility,^7 24 25^ effective management of staff,^24 25^ reduced bureaucracies in procurement and recruitment, increased community awareness of services implementation of planned activities,^7 26^ increased access and use of facility funds,^7 26^ enhanced predictability on financing,^4^ timely payment of salaries,^4 26^ timely procurement^4 26^ and, finally, effective planning for services.

The expected medium-term outcomes include increased budget responsiveness to needs, enhanced resource mobilisation, increased retention of managers, improved staffing, increased staff motivation,^7 26 27^ reduced absenteeism, increased Human Resources for Health (HRH) productivity,^4 24 25^ improved availability of basic services, reduced stockout of essential medicines, cost consciousness, improved reporting, improved citizen accountability and participation, improved facility management and ordering of medicines and supplies based on need. These medium-term goals should then result in the achievement of the following long-term goals: improved access to services, improved quality of services, enhanced facility efficiency, improved sustainable PHC financing, improved accountability, increased client satisfaction, increased service demand/utilisation and efficient referrals.^4 7 26 27^

From the literature, the effect of autonomy reforms is subject to context which is determined by institutional, socioeconomic and geographic factors.^12^ As such, we will monitor constraints that are likely to influence the effectiveness of the reform including weak legislation, dysfunctional boards/committees, limited decision space, political pressures, cash disbursement delays and poor preparation/training.^4 8^

Finally, autonomy reforms may have unintended negative consequences including increased cost of services, misappropriation of funds, ignoring basic services that do not generate revenue, over-reliance on user fees, reshaping quality based on ability to pay, lower quality of goods and services, increased facility debts and increased out of pocket payments. We will monitor the possible unintended consequences and document the efforts by counties to mitigate them.

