#### Sample size and sampling

There will be three levels of sampling for this study. The first level is county sampling, where we will purposively sample four counties already implementing autonomy reforms, four planning to implement the intervention and four not implementing as control. From the sampled counties, we will randomly sample 80 health facilities per group, assuming a mean difference of 10% in facility readiness between the two groups and a population variance of 400 across the groups using 80% power, 95% confidence level and a design effect of 1.2. Because the autonomy reforms have the biggest effects on facilities that raise revenue, we will sample all facilities from levels 4–6 from the selected counties. Leve 4-6 facilities are allowed by law to charge user fees. For the remaining facilities, we will then randomly sample levels 2 and 3. The numbers will be proportionate, targeting a maximum 20 facilities per county. For clients, we will randomly sample a minimum of 1600 clients exiting the health facilities per group, assuming a mean difference of 10% in client satisfaction between the two groups and a population variance of 55 across the groups using 80% power, 95% confidence level and a design effect of 3. To calculate the variance, we took an average of the outcome of the interest in the control and intervention (expected).^28^,^30^ We divide the 1600 clients equally among the selected facilities to achieve a minimum sample of 20 per facility as is recommended for cluster randomised trials.^28 30^ The following sample size calculation formula was used:

,$$n=\left(Z_{\alpha /2}+Z_{\beta \;}\right)sqrd\times 2\times \;\sigma^{2}\;/d^{2}$$

where Z_α/2_=1.96 (5% significance), Z_β_=0.84 (80% power), σ^2^=population variance of 59 (SD of 19 per group) and d=mean difference of 8% between the two groups.

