#### Data collection

We will use trained research assistants to collect data using structured questionnaires on a web-based electronic platform. These questionnaires will be administered in the period preceding and 12 months after the roll-out of autonomy reforms. The health facility questionnaire will be administered to the health facility in charge and other health workers with information on the various sections. It will collect data on the facility profile, target population, services provided, availability of medicine, availability of laboratory services, availability of basic equipment and service utilisation (online supplemental table 1). The health facility assessment questionnaire will evaluate the impact of autonomy on service availability, access to basic equipment, availability of medicines, service utilisation and facility financing (see online supplemental table 1). The client exit interview tool will measure the effects of health facility autonomy on some subjective and objective indicators around service availability and client satisfaction. The exit interviews will seek to establish whether health facility autonomy influences the availability of services and client satisfaction. It will entail questions about the services sought, whether the clients received the services, the client’s perspective on the cost of services, the client’s perspective on facility cleanliness and health worker attitude, how often the clients visit the health facility and whether clients are satisfied with the services (online supplemental table 1).

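### Exit-interview eligibility requires that a service was received, which conflicts with sampling exiting clients and with asking whether the service sought was obtained

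*Protocol article*

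**What the plan says.** All references are to the quantitative component of the protocol article.

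- **Study population** defines clients by receipt twice. The general statement is "We intend to assess selected counties, selected facilities and clients receiving services from the selected facilities". The exit-interview population is then "all patients or carers whose patients had received services from the selected facilities on the day and time of the survey". The next sentence begins "These will include patients or carers seeking services such as outpatient services, antenatal services, postnatal services, child welfare services".
- **Sample size and sampling** sets no receipt condition: "we will randomly sample a minimum of 1600 clients exiting the health facilities per group".
- **Data collection** gives the purpose: "The exit interviews will seek to establish whether health facility autonomy influences the availability of services and client satisfaction". On content it says: "It will entail questions about the services sought, whether the clients received the services".
- **Theory of change** lists among the expected medium-term outcomes "improved availability of basic services, reduced stockout of essential medicines", together with less absenteeism. Better access is a long-term goal. Higher service costs and out-of-pocket payments are listed as possible unintended harms.
- **Primary study design** makes facility readiness the primary outcome. **Data analysis** names service utilisation and client satisfaction as the outcomes of the difference-in-differences (DiD) regression, with the facility as the unit of analysis.

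**The concern.** The population definition requires receipt of a service, while the interview is meant to find out whether the service was received. Someone who leaves unserved because staff were absent, the service was not offered or the fee was too high is one of the exiting clients. The receipt question is plainly about that person, yet the population definition excludes them.

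This is more than untidy wording, because receipt lies on the reform's own causal path. Better availability would bring previously unserved people into the eligible population; higher charges could push some out. Either shift can occur in intervention counties between baseline and endline and not in control counties. DiD removes fixed differences between groups and shared time trends. It does not remove a group-specific change in who is eligible. The fallback cross-sectional comparison is exposed too, since implementing and control counties may differ in the share of clients served.

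**Working it through.** **1. Is a stated figure at stake?** No. The only figure tied to this population is 1600 clients per group, which equals 80 facilities × 20 clients. It does not depend on who counts as a client, and the point does not rest on it.

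**2. Do the sections agree on an unserved client?**

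| Section | Condition on the client | Is a wholly unserved client in? |
|---|---|---|
| Study population, general statement | receiving services | no |
| Study population, exit interviews | had received services | no |
| Study population, following sentence | seeking listed services, but it refers back to the group just defined | no, read strictly |
| Sample size and sampling | exiting the facility | yes |
| Data collection | asked whether the service sought was received | yes, by implication |

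No section expressly admits a client who received nothing.

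**3. What follows by construction.** If eligibility requires receipt, the proportion who received any service is 100% in each group at each wave. The DiD on that proportion is (100 − 100) − (100 − 100) = 0, whatever the reform does. Receiving some but not all of what was sought can still vary.

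**4. Illustration for satisfaction.** The document gives no unserved share and no satisfaction score by receipt, so every input here is an assumption. Let the unserved share go from u0 to u1 in the intervention arm and stay constant in the control arm. Let mean satisfaction be s = 75 for clients served at both waves, t = 30 if unserved, and m for clients who become served because of the reform.

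- Change among everyone leaving = (u0 − u1)(m − t)
- Change among served clients only = (u0 − u1)(m − s)/(1 − u1)

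| Assumed case | Everyone leaving | Served only |
|---|---|---|
| 20% to 10%, m = 60 | 66.0 to 69.0 (+3.0) | 75.0 to 73.3 (−1.7) |
| 20% to 10%, m = 75 | 66.0 to 70.5 (+4.5) | 75.0 to 75.0 (0) |
| 5% to 2.5%, m = 60 | 72.75 to 73.5 (+0.75) | 75.0 to 74.6 (−0.4) |
| 10% to 20% (first case reversed) | 69.0 to 66.0 (−3.0) | 73.3 to 75.0 (+1.7) |

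First row in full. Everyone leaving: 0.8×75 + 0.2×30 = 66.0, then 0.8×75 + 0.1×60 + 0.1×30 = 69.0. Served only: 75.0, then (0.8×75 + 0.1×60)/0.9 = 73.3.

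The second formula shows that the sign of the served-only change depends on whether m lies below or above s. The fourth row shows the distortion running the other way when access worsens. For scale, the Sample size section plans on a satisfaction difference of 10% (8% beneath the formula). The gap between the two columns is 4.7 points in the first row and about 1.1 in the third.

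**The case against.** **Loose wording is plausible.** The words for seeking and exiting, and the receipt question itself, all suit a frame of everyone leaving. Screening rules may also sit in a fuller document. This stands as a reading of intent, and it is why the point is not evidence of a deliberate design error. But the article states the receipt condition twice, and interviewers who follow it would screen out unserved clients.

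**The main results are largely untouched.** This stands. Readiness is measured on facilities. The facility questionnaire covers availability, medicines, utilisation and financing, and the interrupted time series uses DHIS data. None of these depends on client eligibility.

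**Satisfaction among people who received care is a coherent quantity.** It is, if stated as the target. The article instead uses the interview to judge availability as well, which a served-only population can do only in part.

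**Attendance also responds to the reform.** This stands. Sampling everyone who leaves narrows the selection but does not end it, because people deterred before arrival are missed either way.

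Two stronger readings are tempting. A reader might infer that exclusion through cost becomes invisible to the study. It does not: the interview asks clients about cost, the facility tool covers financing and utilisation, and the process evaluation documents unintended consequences. A reader might also infer that the exit interview cannot measure availability at all. It can, for partial non-receipt such as a consultation without the medicine, and stockouts may well appear in that form.

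**Conclusion.** The sections conflict and need correcting. As written, complete denial of service cannot be recorded in the exit interviews. Client satisfaction and client-reported availability are conditioned on a variable that the reform may change differently by group and wave.

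Severity is moderate. Client satisfaction is a DiD outcome and the basis of the client sample size, but it is not the primary outcome.

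Neither the size nor the direction of any bias can be derived from the document. A reader might take the first illustrative row to show that the estimated effect will reverse sign. That reversal rests entirely on scoring newly served clients below those already served: with equal scores the served-only change is 0, and with few unserved clients the distortion is about a point. What needs no assumed scores is that receipt of any service is fixed at 100%.

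**What to change.** In Study population, define exit-interview clients as all patients or carers leaving a selected facility after seeking one of the listed services, whether or not they received it, and sample them at the facility exit. Record the reason for non-receipt (stock, staff, cost, referral). Include these clients in the availability and satisfaction means, and report a served-only analysis as secondary. Apply the same rule in all groups and both waves.

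The study began in January 2023, and the article does not say whether baseline interviews are complete. If they were done on served clients only, widening eligibility at endline alone would make the waves non-comparable. In that case keep the satisfaction DiD served-only, report the unserved share separately, and state the limitation.

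The cost is one sentence of eligibility text plus interviewer training. The receipt question already exists and the target of 1600 need not change. Unserved clients would take up part of it: at an assumed 5% or 20% unserved, 1600×0.95 = 1520 or 1600×0.80 = 1280 would remain for the served-only analysis. The other downsides are some short interviews with people who can say little about quality of care, and that people deterred before arrival are still not captured.

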#### Sample size and sampling

There will be three levels of sampling for this study. The first level is county sampling, where we will purposively sample four counties already implementing autonomy reforms, four planning to implement the intervention and four not implementing as control. From the sampled counties, we will randomly sample 80 health facilities per group, assuming a mean difference of 10% in facility readiness between the two groups and a population variance of 400 across the groups using 80% power, 95% confidence level and a design effect of 1.2. Because the autonomy reforms have the biggest effects on facilities that raise revenue, we will sample all facilities from levels 4–6 from the selected counties. Leve 4-6 facilities are allowed by law to charge user fees. For the remaining facilities, we will then randomly sample levels 2 and 3. The numbers will be proportionate, targeting a maximum 20 facilities per county. For clients, we will randomly sample a minimum of 1600 clients exiting the health facilities per group, assuming a mean difference of 10% in client satisfaction between the two groups and a population variance of 55 across the groups using 80% power, 95% confidence level and a design effect of 3. To calculate the variance, we took an average of the outcome of the interest in the control and intervention (expected).^28^,^30^ We divide the 1600 clients equally among the selected facilities to achieve a minimum sample of 20 per facility as is recommended for cluster randomised trials.^28 30^ The following sample size calculation formula was used:

,$$n=\left(Z_{\alpha /2}+Z_{\beta \;}\right)sqrd\times 2\times \;\sigma^{2}\;/d^{2}$$

where Z_α/2_=1.96 (5% significance), Z_β_=0.84 (80% power), σ^2^=population variance of 59 (SD of 19 per group) and d=mean difference of 8% between the two groups.

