### Evaluating the effects of autonomy reforms

#### Primary study design

We will employ a before and after quasi-experimental study to measure the effects of health facility autonomy on health facility readiness, functionality, service utilisation and client satisfaction of health facility autonomy reforms. We will conduct an assessment before implementation of the FIF reforms and an assessment after 12 months of implementation of the FIF reforms. The primary outcome of interest will be health facility readiness.

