#### Secondary study design

There are uncertainties about the roll-out of autonomy, with possibilities that might compromise the proposed study design (quasi-experimental before and after design). The pace of autonomy reforms roll-out could be slow, with the implication that the selected intervention counties do not convert to intervention counties (ie, autonomy reforms are not implemented in these counties over the 12-month study period). To mitigate this, we will sample four additional intervention counties that have already implemented autonomy reforms. We will use a cross-sectional study design comparing these four counties that are already implementing autonomy, with the counties that do not have autonomy (control counties). This design will also ensure that we can measure effects in the event the time of the study is not sufficient to measure effects within counties that are just rolling out autonomy.

Further, we will use an ITS design to evaluate the effects of the reforms in the counties that will have rolled out the reforms across the country. We will collect and analyse monthly District Health Information System (DHIS) data on key performance indicators from PHC facilities across selected counties in Kenya, spanning 24 months before the introduction of autonomy reforms in a county and 24 months after its introduction. Exact times for pre-intervention and post-intervention phases will vary based on the exact time that autonomy reforms were introduced in a county.

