#### Data analysis

We will compute means, medians and SD of all study variables and key sample characteristics at the baseline and end line. To determine the effects of autonomy reforms on service utilisation and client satisfaction, we will use the quasi-experimental difference-in-difference (DiD) analysis. We will first compute the differences in means between the baseline and end line for each study group, then the differences in mean between the intervention and control.

Thereafter, we will estimate the effect using multivariate regression analysis. This means that we will calculate the DiD while controlling for other covariates that are likely to affect outcomes such as facility average insurance coverage, average distance to facility for facility catchment population, health worker density and facility size. The unit of analysis will be the health facility, and the outcomes of interest will be service utilisation and client satisfaction.

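### The 80% power for 80 facilities per group comes from a single-time-point formula and is not established for the two-wave difference-in-differences; it holds only if the baseline–endline correlation is at least about 0.47, and none is given

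*Protocol article*

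**What the plan says.** All references are to the Protocol article, under Evaluating the effects of autonomy reforms unless noted.

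- **Sample size and sampling:** the number of facilities is fixed by the sentence "From the sampled counties, we will randomly sample 80 health facilities per group". The inputs behind that number are stated as "assuming a mean difference of 10% in facility readiness between the two groups and a population variance of 400 across the groups using 80% power"; a 95% confidence level and a design effect of 1.2 complete them. The printed formula is n = (Z_α/2 + Z_β)² × 2 × σ² / d². It has no term for a second wave and none for a correlation between waves. The values listed beneath it are a variance of 59, an SD of 19 and a difference of 8%.
- **Primary study design:** readiness is the primary outcome, and there are two assessments: "We will conduct an assessment before implementation of the FIF reforms and an assessment after 12 months of implementation of the FIF reforms".
- **Secondary study design:** the first fallback is a cross-sectional comparison of four already-implementing counties with the control counties.
- **Abstract, Methods and analysis:** difference-in-differences is the analysis for the quantitative component as a whole.
- **Data analysis:** the estimate is built up in this way: "We will first compute the differences in means between the baseline and end line for each study group, then the differences in mean between the" two arms. A covariate-adjusted regression follows, with the facility as unit of analysis. This section names only service utilisation and client satisfaction as outcomes. Readiness comes under difference-in-differences through the abstract and the Primary study design section.

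**The concern.** The article states a formula, its inputs and a power, and the formula does not belong to the analysis it calls primary. A single-wave comparison of two means carries the sampling error of two group means. A difference-in-differences carries that of four, reduced by however strongly each facility's two scores are correlated. The two variances coincide only at one value of that correlation.

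This goes beyond a detail left to an analysis plan, because the article makes an unqualified power claim. At stake is how a null result is read. A non-significant difference-in-differences would be taken as evidence against a 10-point effect from a study with 80% power, when the power for that contrast could be well below or well above 80%.

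**Working it through.** **Inputs from Sample size and sampling:** σ² = 400 (SD 20), d = 10, two-sided 5% (Z = 1.96), 80% power (Z = 0.84), design effect 1.2, 80 facilities per group.

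**Assumptions not in the document:** ρ (shown as a range), equal variance at both waves, the design effect of 1.2 applied unchanged to the change contrast, and no precision gained from covariates.

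**1. The plan's own figure.** (1.96 + 0.84)² × 2 × 400 / 10² = 7.84 × 8 = 62.7. Multiplied by 1.2 this is 75.3, or 76 per group. The stated 80 is slightly higher and equals 4 counties × 20. At 80 per group the effective number is 80 / 1.2 = 66.7, the standard error is √(2 × 400 / 66.7) = 3.46, and power is Φ(10 / 3.46 − 1.96) = 82%. The number is sound for a single-wave comparison.

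**2. The primary contrast.** With the same facilities at both waves, the variance of one facility's change is 2σ²(1 − ρ). The difference between two groups' mean changes has variance 4σ²(1 − ρ)/n, against 2σ²/n in the printed formula. They are equal only at ρ = 0.5.

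Standard error = √(1600(1 − ρ) / 66.7); power = Φ(10 / SE − 1.96); detectable difference at 80% power = 2.80 × SE; facilities needed = 7.84 × 4 × 400 × (1 − ρ) / 100 × 1.2 = 150.5 × (1 − ρ), rounded up.

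| ρ | SE | Power, 80 per group | Detectable difference | Facilities per group for 80% |
|---|---|---|---|---|
| 0 | 4.90 | 53% | 13.7 | 151 |
| 0.2 | 4.38 | 63% | 12.3 | 121 |
| 0.3 | 4.10 | 68% | 11.5 | 106 |
| 0.4 | 3.79 | 75% | 10.6 | 91 |
| 0.5 | 3.46 | 82% | 9.7 | 76 |
| 0.6 | 3.10 | 90% | 8.7 | 61 |
| 0.7 | 2.68 | 96% | 7.5 | 46 |

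**3. Break-even.** 80% power needs SE = 10 / 2.80 = 3.57, so 24(1 − ρ) = 12.75 and ρ is about 0.47.

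**4. If the standard error ignored the pairing.** The test would use SE = 4.90 whatever ρ is, so it rejects beyond 1.96 × 4.90 = 9.60. Power is Φ((10 − 9.60) / true SE): 53% at ρ = 0, 55% at 0.5 (true SE 3.46) and 57% at 0.8 (true SE 2.19).

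**5. Sensitivity to the design effect.** With no design effect the linked power is 61% at ρ = 0, 76% at 0.3 and 82% at 0.4. It still depends on ρ.

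**6. The inputs under the formula.** An SD of 19 is a variance of 361, not 59, and neither matches 400; a difference of 8 does not match 10. Variance 361 with d = 8 gives 88.4, or 106.1 after the 1.2 design effect. Variance 59 with d = 8 gives 14.5, or 17.3. Neither set yields 80.

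**The case against.** A reader might infer that the study really has only 53–57% power. The documents do not support that. The figure requires either waves that are uncorrelated or nearly so, or a standard error that ignores the pairing together with covariates that explain nothing. The article states none of these.

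The evidence points towards revisited facilities. One facility sample is described, and the questionnaires are given before and 12 months after roll-out. All level 4–6 facilities are taken; by Table 1 that is 26 in the control counties and 34 in the intervention counties, or 33% and 43% of each group's 80. Apart from openings and closures, those would be the same facilities at both waves, so ρ is probably positive.

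Nor does building the estimate from group means show that the pairing is ignored. With the same facilities at both waves, the difference of group means equals the mean of the facility changes. The variance estimator is something a condensed article may leave to a fuller document. Covariates could also help: if they explained an assumed 30% of readiness variance, the unlinked standard error would be 4.10 (68% power at ρ = 0), and at 50% it would be 3.46 (82%). Differencing also removes stable county effects, so 1.2 may be too large for this contrast.

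These points stand, and they rule out a single low figure. They do not supply the missing justification: the printed formula remains the wrong one for the primary contrast, and the quantity that decides its power is not stated.

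**Conclusion.** The concern holds as a statement about what has been shown. The 80% power is not established for the primary two-wave analysis of readiness. With linked facilities it ranges from 53% (ρ = 0) to 96% (ρ = 0.7) and meets the claim only if ρ is at least about 0.47. It would be wrong to say that the study is underpowered; at a higher ρ it exceeds its target.

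The figures use variance 400 and a difference of 10, which are the values given for readiness, and rest on the assumptions listed in the working. They would shift if the conflicting values under the formula were the intended ones. That readiness is analysed by difference-in-differences is read from the abstract and the Primary study design section, since the Data analysis section does not name it.

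**What to change.** Keep 80 facilities per group.

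1. **Sample size and sampling.** For the primary design use n = (Z_α/2 + Z_β)² × 4 × σ² × (1 − ρ) / d² × design effect. Replace the unqualified 80% with the power, or the detectable difference, for 80 facilities over a stated range of ρ (for example 0.2 to 0.7). Keep the present formula for the cross-sectional fallback only. Reconcile the variance of 59, SD of 19 and difference of 8 with the variance of 400 and difference of 10.
2. **Data analysis.** Name readiness as an outcome of the difference-in-differences. State that the same facilities are assessed at both waves. Analyse facility-level change, or fit facility fixed effects, so that the standard error uses the within-facility correlation.

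The cost is rewording two sections and a change to the model specification, with no extra facilities or data. The stated power becomes less favourable if ρ is below about 0.47. Covariates that do not change between waves, such as distance to the facility, drop out of a fixed-effects model.

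### Taking every hospital into samples of 80 gives a level mix that differs by arm and is far from the stated population, and the described analysis has no facility-level term

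*Protocol article*

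**What the plan says.** **Population.** Under Study population, "the study population will be all county-owned public facilities within the selected counties across all level 2-6". Table 1 lists 1,430 such facilities in the 12 counties, of which 96 are level 4, 4 are level 5 and none are level 6.

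**Sampling.** Under Sample size and sampling, "we will randomly sample 80 health facilities per group", and "we will sample all facilities from levels 4–6 from the selected counties". The reason given is that the reforms should act most strongly where facilities earn their own revenue, and levels 4–6 may charge user fees. Levels 2 and 3 are drawn at random for the remaining places. On the allocation: "The numbers will be proportionate, targeting a maximum 20 facilities per county".

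**Analysis.** Under Data analysis, "We will first compute the differences in means between the baseline and end line for each study group", and these are then compared between intervention and control. A multivariate DiD regression follows, with the facility as unit. Its example covariates are insurance coverage, distance, health worker density and facility size. Neither step mentions facility level, strata or sampling weights.

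**Fallback.** Under Secondary study design, if roll-out is slow, the four already-implementing counties are compared cross-sectionally with the four controls.

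**The concern.** Taking every hospital while fixing the total at 80 leaves levels 2 and 3 with whatever places remain. The number of hospitals differs between counties and groups, so the level mix does too. Two things follow.

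- **Meaning of the pooled effect.** The plan expects the effect to depend on facility level. A pooled estimate then depends on the level mix, and this mix comes from the take-all rule and the cap rather than from the stated population.
- **Comparability of the arms.** The mix differs between the groups being compared. Stable differences between levels cancel in a DiD, but different time trends by level do not. In a cross-sectional comparison nothing cancels.

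**Working it through.** **The plan's own figure.** For facilities the plan targets a readiness difference of 10 points; its other inputs are "a population variance of 400 across the groups using 80% power, 95% confidence level and a design effect of 1.2". The plan's formula gives (1.96 + 0.84)² × 2 × 400 / 10² = 62.7, and × 1.2 = 75.3, so 76. The stated 80 is slightly larger and equals 4 counties × 20. (The legend under the formula, "population variance of 59 (SD of 19 per group) and d=mean difference of 8% between the two groups", carries other inputs and does not yield 80. It plays no part below.)

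**Level mix from Table 1** (hospitals = levels 4 + 5; there are no level 6 facilities)

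| Group | Hospitals by county | Total | Share of 80 | Facilities in counties | Share there |
|---|---|---|---|---|---|
| Control | 3 + 14 + 5 + 4 | 26 | 32.5% | 375 | 6.9% |
| Intervention | 13 + 3 + 16 + 2 | 34 | 42.5% | 471 | 7.2% |
| Already implementing | 12 + 5 + 18 + 5 | 40 | 50.0% | 584 | 6.8% |

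Overall, 100 / 1,430 = 7.0%. The group shares need only the take-all rule and a total of 80.

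**Within counties.** Reaching 80 from four counties with at most 20 each requires exactly 20 per county. Level 2–3 places are then 20 minus the county's hospitals: 2 for 166 facilities in Nakuru, 4 for 168 in Homabay, 7 for 159 in Kakamega, but 17 for 32 in Lamu. On these numbers, proportionate allocation can describe only the split between levels 2 and 3.

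**Primary DiD.** Suppose the reform has no effect, and hospitals change by tH and levels 2–3 by tL in both arms. The DiD of means is (0.425 − 0.325) × (tH − tL) = 0.10 × (tH − tL). For assumed trend differences of 10 and 20 points this is 1 and 2 points. If the same facilities are measured in both waves, an additive size covariate that does not change over time leaves this unchanged, because such a covariate is orthogonal to the group-by-time term.

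**Cross-sectional fallback.** With a readiness gap g between levels, the unadjusted spurious difference is (0.50 − 0.325) × g = 0.175 × g. The documents do not give g. For assumed gaps of 10, 20, 30 and 40 points the result is 1.75, 3.5, 5.25 and 7.0 points, against a target difference of 10.

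**Meaning of the pooled effect.** With effects of 10 in hospitals and 2 in levels 2–3 (assumed, for illustration), the intervention-sample mix gives 0.425 × 10 + 0.575 × 2 = 5.4. The mix in the counties gives 0.072 × 10 + 0.928 × 2 = 2.6.

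**Precision by level**, on the plan's single-wave inputs: for levels 2–3, SE = √(400 × 1.2 × (1/46 + 1/54)) = 4.4, so the detectable difference is 2.8 × 4.4 = 12.3 points. For all 80 per arm, √(480 × 2/80) = 3.5 and 2.8 × 3.46 = 9.7. These carry over to a DiD only if the within-facility correlation is about 0.5, since the variance of a change is 2 × 400 × (1 − ρ).

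**Full design weights.** Hospitals have weight 1; level 2–3 facilities have weight (facilities in county) / (places). The effective number is (Σw)² / Σw².
- Intervention: 471² / (34 + 159²/7 + 32²/17 + 168²/4 + 78²/18) = 221,841 / 11,100 = 20.
- Control: 375² / (26 + 49²/17 + 134²/6 + 97²/15 + 69²/16) = 140,625 / 4,085 = 34.

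**The case against.** Four points can be made for the plan.

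- **The oversampling is deliberate.** The plan gives its reason, and the Background counts first referral hospitals as part of facility-based primary care. This stands: a reader might infer that hospitals do not belong in a primary care study, and the documents say otherwise. But a good reason to oversample hospitals does not settle which facilities the pooled effect describes.
- **The article does not say that the analysis is unweighted.** Group means are only the first step, the regression follows, and its covariate list is open. This also stands. A reader might infer a decision to rely on pooled unweighted means, but the text only leaves level and weights unmentioned, and a fuller plan might supply them. What remains is that the population, the sampling rule and the estimator as described do not fit together.
- **Facility size is a proxy for level.** This stands in part. As a main effect it could absorb some of a static readiness gap in the fallback, for which the article states no model. It removes neither level-specific trends nor level-specific effects in the DiD.
- **Standardising by level does not recover the Table 1 population.** This is correct. Lamu and Nyandarua supply 17 + 18 = 35 of the 46 intervention level 2–3 places (76%) but hold only 32 + 78 = 110 of 437 such facilities (25%). The fix has to acknowledge this.

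**Conclusion.** The point holds as a mismatch between stated population, sampling and described model. Hospitals are 32.5%, 42.5% and 50% of the three samples against about 7% of the population. The described DiD has no level term, although the plan expects the effect to vary by level.

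The sizes differ by design. The primary DiD is exposed only to differing trends, at 0.10 times the trend difference. The 1.75 to 7 points apply to the fallback alone, before any adjustment, and rest on assumed gaps of 10 to 40. The readiness scale is used because readiness is the primary outcome and has the stated facility-level target; the Data analysis section itself names utilisation and satisfaction, so applying the same DiD to readiness is an assumption.

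Two stronger readings are not supported. One is that the pooled result is mostly a hospital effect: hospitals are a minority in both primary arms (26 + 34 = 60 of 160) and exactly half in the already-implementing group. The other is that the primary DiD is seriously biased: 1 point for a 10-point trend difference is small beside a target of 10.

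This is a cheap improvement, not a fault that undermines the design.

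**What to change.** No resampling is needed.

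1. In the DiD, include facility level (2–3 versus 4–6) with level-by-time and level-by-treatment-by-time terms and their lower-order terms.
2. Make the separate levels 2–3 and levels 4–6 effects the main presentation.
3. Adjust the cross-sectional comparison for level.
4. For any pooled effect, apply one fixed level mix to both arms and say that it represents that mix, not the Table 1 population. If an estimate for that population is wanted, add county-by-level design weights as a sensitivity analysis.

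The change costs only wording in the analysis section, but precision falls. The levels 2–3 effect rests on 46 versus 54 facilities (SE about 4.4; about 12 points detectable, against a planned 10). The design-weighted sensitivity analysis would have only about 20 (intervention) and 34 (control) effective facilities of 80 and should be read accordingly.
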